### Sample Size Calculation

Sample size calculation is based on the known mean value and SD of the SPFLS (food literacy measure) for the Dutch general population [36]. There are no RCTs with lifestyle interventions in the scientific literature that assessed food literacy (measured with SPFLS or another measure for food literacy) as a primary outcome. However, as RCTs evaluating lifestyle interventions that targeted psychosocial outcomes such as self-efficacy have demonstrated effect size of between 1.1 and 1.7 [48,49], it seemed reasonable to expect an effect size of 0.9. With use of the Cohen *d* calculation for effect size, an anticipated mean of 4.20 SPFLS score in the intervention group, and an anticipated mean of 3.83 (SD 0.41) in the control group is expected at T1 (based on references values [36]). With a standard power of 80% and a significance level of 5%, a total of 19 participants per group (38 participants in total) are needed. Adding a 30% dropout rate, the ideal sample size was set at 28 participants per group (56 in total).

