### Statistical Analyses

Statistical analyses are carried out using IBM SPSS Statistics for Windows, version 28 (released in 2021; IBM Corp). Two-sided *P* values <.05 are regarded as statistically significant. Analyses are performed with the intention-to-treat principle, meaning that all patients were analyzed in their original allocation group regardless of the extent to which they followed the intervention. Dropouts are counted, and reasons for dropping out are recorded. If missing is completely at random, all available data at T0 (baseline), T1 (12 weeks), and T2 (24 weeks) are used to conduct the analyses. If missing is at random, multiple imputation techniques are used to impute the missing data.

Scores are calculated for multiple-item instruments (ie, DGSES, WHOQOL-BREF, SoC-13, DHD-15 index, and SPFLS). Randomization will be checked, and variables will be normalized if needed. Descriptive statistics are performed to tabulate mean (or median) values of all study characteristics and baseline values of the independent variables. Chi-square tests (for categorical variables) and 2-tailed *t* tests (for continuous variables) are used to compare the descriptive statistics between study groups and to identify potential covariates. Data are tabulated as mean (SD) or median (IQR) if skewed. Categorical data are presented as n (%) where appropriate.

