According to a strict data analysis protocol, primary and secondary outcomes are tested with mixed models. Secondary outcomes are also tested if the primary outcome is not statistically significant. The analyses scripts will be written by the researchers; the analysis of the primary outcome will be run by an independent researcher who is blind to the intervention code. Assumptions for mixed models are checked. The mixed models will test the difference compared with baseline in the scores and values (ie, dependent variables) between intervention and control (ie, independent variable) at T1 and T2. Fixed effects are the treatment condition, time, and the covariates; random effects are the repeated measures per participant at T0, T1, and T2. Multiple models are tested; a crude model, and additional models that are adjusted for confounders commonly adjusted for in literature (eg, sex, age, education, and BMI). Variables that statistically significantly differed at baseline are also included in a model as covariates. The final results are presented in a table displaying the estimated marginal means, 95% CIs, and *P* values for the treatment effect for all primary and secondary outcomes.

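### The fixed effects listed for the mixed model omit the treatment-by-time term that the stated comparison with baseline at T1 and T2 requires

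*Protocol article*

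**What the plan says.** All of the following comes from the protocol article.

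- **The test.** Under Statistical Analyses: "The mixed models will test the difference compared with baseline in the scores and values", with the comparison made "between intervention and control (ie, independent variable) at T1 and T2".
- **The model.** The same paragraph continues: "Fixed effects are the treatment condition, time, and the covariates; random effects are the repeated measures per participant at T0, T1, and T2".
- **The data.** If data are missing completely at random, "all available data at T0 (baseline), T1 (12 weeks), and T2 (24 weeks) are used to conduct the analyses".
- **The report.** The results table is to show "estimated marginal means, 95% CIs, and *P* values for the treatment effect for all primary and secondary outcomes". No time point is attached to the treatment effect.
- **The sizing.** Under Sample Size Calculation the plan assumes that the SALUD arm will average 4.20 on the SPFLS. For the comparator it states: "an anticipated mean of 3.83 (SD 0.41) in the control group is expected at T1". The target is therefore a between-arm difference at T1.

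No treatment-by-time interaction is mentioned anywhere in the article.

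**The concern.** When T0 is one of the repeated outcomes, a difference between arms in change from baseline is a treatment-by-time contrast. A model with only main effects of treatment and time forces the arm difference to be the same at all three visits. It returns one number for treatment, which has three faults:

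- It includes T0, where randomisation makes the expected difference zero. The estimate is pulled toward zero if the effect is similar at T1 and T2 or fades.
- It carries any chance difference at T0 into the treatment effect instead of removing it.
- It cannot give one answer for T1 and another for T2, although the plan promises both and the sample size rests on T1.

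The same model serves the primary outcome and every secondary outcome. The scripts are written by the researchers, and an independent blinded researcher runs the primary analysis, so the written list of terms matters.

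**Working it through.** **Inputs from the protocol.** T1 means 4.20 and 3.83, SD 0.41; two-sided 5% level, 80% power; 19 per group before and 28 after a 30% dropout allowance.

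**Assumed, because the protocol does not give them.** Within-person correlation ρ of 0.3 to 0.7; T2 effect from 0 to 2 times the T1 effect; the covariance structure.

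**1. The plan's own figure.** The difference is 4.20 − 3.83 = 0.37, and 0.37/0.41 = 0.90, as stated. By the normal formula, n = 2 × (1.96 + 0.842)² × (0.41/0.37)² = 19.3 per group. The plan's 19 gives 79.4% power by that formula and 77.2% by the t test. Then 19/0.7 = 27.1, rounded up to 28. The stated size reproduces closely, and it is the size for a T1 difference.

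**2. What the listed model estimates.** With treatment and time as main effects, the treatment coefficient is a weighted mean of the arm differences at T0, T1 and T2. The weights are V⁻¹1/(1′V⁻¹1), where V is the within-person covariance. With complete data, equal variances and compound symmetry, each weight is 1/3:

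| Effect at T2 | Expected coefficient | Share of 0.37 |
|---|---|---|
| Sustained | (0 + 0.37 + 0.37)/3 = 0.247 | 67% |
| Half remains | (0 + 0.37 + 0.185)/3 = 0.185 | 50% |
| None remains | (0 + 0.37 + 0)/3 = 0.123 | 33% |
| 1.5 times T1 | (0 + 0.37 + 0.555)/3 = 0.308 | 83% |
| 2 times T1 | (0 + 0.37 + 0.74)/3 = 0.370 | 100% |

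Other structures, with a sustained effect:

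- AR(1), ρ 0.3 to 0.7: 63% to 57% survives.
- T0 SD 30% larger, unequal variances modelled, ρ = 0.5: 91% (compound-symmetric correlations) or 81% (AR(1)).
- T0 SD 20% smaller, ρ = 0.5, compound-symmetric correlations: 41%.
- 28 per arm, 30% of participants with T0 only, ρ = 0.5 (250 simulated trials, random-intercept model): 51%.

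In 250 simulated complete-data trials at 19 per group and ρ = 0.5, the main effect averaged 0.248 and the T1 interaction 0.376.

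**3. Baseline imbalance.** At 28 per arm the standard error of the T0 difference is 0.41 × √(2/28) = 0.110. Under compound symmetry a T0 difference d shifts the expected coefficient by d(1 + 2ρ)/3. At ρ = 0.5, a chance imbalance of one standard error moves it by 0.110 × 2/3 = 0.073.

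**4. Power with a sustained effect, complete data and compound symmetry.** Standard errors, each multiplied by 0.41 × √(2/n):

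- main effect: √((1 + 2ρ)/3)
- T1 change contrast: √(2(1 − ρ))
- baseline-adjusted T1: √(1 − ρ²)

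Two-sided t test:

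| n per arm | ρ | Main effect (0.247) | T1 change (0.37) | Baseline-adjusted T1 (0.37) |
|---|---|---|---|---|
| 28 | 0.3 | 85.7% | 80.0% | 93.5% |
| 28 | 0.5 | 77.3% | 91.2% | 96.9% |
| 28 | 0.7 | 69.6% | 99.0% | 99.6% |
| 19 | 0.3 | 69.5% | 62.8% | 80.9% |
| 19 | 0.5 | 59.9% | 77.2% | 87.7% |
| 19 | 0.7 | 52.3% | 93.7% | 96.6% |

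At 28 per arm and ρ = 0.5, simulation (4,000 trials) gave 78% for the main effect and about 91% for the T1 change contrast. If half or none of the effect remains at T2, the main-effect figure falls to 52.8% or 27.3%.

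**The case against.** The sentence before the list of terms states the intended comparison plainly. A reader might infer that the trial will certainly report a diluted effect, and the text does not settle that. The wording on random effects is not a literal model specification either, so the list may name factors and not every term. The article also refers to a data analysis protocol and scripts that are not shown. A further reading takes change from baseline as the dependent variable, in which case T0 dilutes nothing. These points limit confidence in the literal reading, but they do not remove the contradiction. The terms are stated, not left out. T0 is named among the repeated measures, and change from baseline at T0 would be zero for everyone.

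It is also tempting to say that at least a third of the effect is lost. That is not a bound. The loss is one third only with complete data, equal variances, compound symmetry and equal effects at T1 and T2. It is smaller if the effect grows by T2 or the T0 variance is larger.

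Nor does the listed model always lose power. At ρ = 0.3 with a sustained effect, its test has more power than the raw T1 change contrast (85.7% against 80.0% at 28 per arm). Even at ρ = 0.5, its 77 to 78% at 28 per arm is close to the planned 80%. A baseline-adjusted T1 contrast does better in every row of the power table. The case for change rests mainly on which quantity is estimated, and power is secondary.

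**Conclusion.** The concern holds as an internal contradiction, and the model is wrong as written: the listed terms cannot deliver the comparison that the same paragraph promises. It bears on the primary outcome and every secondary outcome. If the list is followed literally, with complete data, equal variances and compound symmetry, the planned 0.37 becomes about 0.25, 0.185 or 0.12 for a sustained, halved or absent T2 effect. These sizes depend on a T2 effect and a covariance structure, and the power figures also on a correlation, none of which the protocol states. Confidence is high that the two statements conflict, and only moderate that a diluted effect would actually be reported.

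**What to change.** Replace the list of fixed effects by one of these:

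- treatment, categorical time, treatment-by-time and the covariates, with T0, T1 and T2 as outcomes. A common mean for both arms at T0 is an option that amounts to baseline adjustment;
- T1 and T2 as outcomes, with the baseline value as a covariate and treatment-by-time kept so that the two visits can differ.

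Either way, name the T1 contrast as the primary estimate and the T2 contrast as secondary, and have the results table show these contrasts. Adding the interaction is not enough if the reported P value remains the overall treatment test, because that still averages over visits. Use the same model for the secondary outcomes. A constrained baseline or an unstructured covariance is a reasonable choice but is not needed to remove the contradiction.

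The cost is one or two sentences and a small change to the SPSS script (some recoding of terms if the common-baseline form is chosen). No new data are needed.

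### The arm-by-time term that the change-from-baseline contrast needs is not listed, and once it is added, main-effect covariates almost drop out, so the adjusted models largely repeat the crude one

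*Protocol article*

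**What the plan says.** The Statistical Analyses section of the protocol article settles four things.

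- **Contrast.** "The mixed models will test the difference compared with baseline in the scores and values (ie, dependent variables) between intervention and control", at T1 and T2.
- **Terms.** "Fixed effects are the treatment condition, time, and the covariates; random effects are the repeated measures per participant at T0, T1, and T2". T0 is therefore on the outcome side. No interaction of any kind is named.
- **Adjustment.** The models are "a crude model, and additional models that are adjusted for confounders commonly adjusted for in literature (eg, sex, age, education, and BMI"). In addition, "Variables that statistically significantly differed at baseline are also included in a model as covariates".
- **Missing data.** Where values are lost completely at random, every observed score from the three visits is analysed. For the other case considered, the rule is: "If missing is at random, multiple imputation techniques are used to impute the missing data".

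BMI is also a secondary outcome (Quantitative Evaluation). The text does not say whether BMI as a covariate is the baseline value or the value at each visit.

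**The concern.** The listed terms do not match the stated contrast, in two linked ways. First, without an arm-by-time term the model cannot express a between-arm difference in change. Second, adding that term alone leaves the adjustment almost inert. A baseline characteristic entered as a main effect moves all three of a participant's scores by the same amount, and the change from T0 removes it.

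The plan compares the arms at baseline and puts variables that differ into a model, so the adjusted rows of the final table will be read as a check on baseline differences. With 28 per arm, a sizeable chance imbalance is plausible. If crude and adjusted rows agree by construction, a reader may take this as evidence that confounders do not matter, while an imbalance in something that predicts improvement is left where it was.

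**Working it through.** **1. Scale, from Sample Size Calculation.** d = (4.20 − 3.83)/0.41 = 0.37/0.41 = 0.90. By normal approximation, n per arm = 2 × (1.960 + 0.842)² × (0.41/0.37)² = 19.28; the plan has 19. Then 19/0.7 = 27.1, rounded up to 28, as stated. These figures are not in dispute here; they set the scale.

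**2. The list taken literally.** With g for arm and x for a time-fixed covariate, E[Y_t] = a_t + b·g + c·x. The expected change is E[Y_t − Y_0] = a_t − a_0, which contains no arm term. The coefficient b is an arm difference averaged over T0, T1 and T2.

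**3. With arm-by-time added and the arms free to differ at T0.** E[Y_t] = a_t + b_t·g + c·x. The estimate of b_t is (difference in mean Y_t) − c × (difference in mean x). Subtracting, b_t − b_0 = (difference in mean Y_t) − (difference in mean Y_0). Neither c nor x remains.

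**4. Numerical check.** Simulated data with 28 per arm, SD 0.41 and true effects of 0.37 at T1 and 0.30 at T2. Assumed, not in the documents: within-person correlation 0.6, and a covariate imbalanced by 0.5 SD that adds 0.15 points per SD to T1 and T2. Models were fitted by REML. Each row is one data set and shows the T1 effect in SPFLS points.

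| Data | Covariance | Crude | Covariate as main effect | Covariate-by-time added |
|---|---|---|---|---|
| Complete | Compound symmetry | 0.48223 (SE 0.09045) | 0.48223 (SE 0.09045) | 0.422 |
| Complete | Unstructured | 0.48500 (SE 0.10077) | 0.48500 (SE 0.10077) | 0.395 |
| About 30% dropout | Compound symmetry | 0.447 | 0.440 | 0.434 |
| About 30% dropout | Unstructured | 0.404 | 0.405 | 0.303 |

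Over 8 further data sets per structure with dropout, the largest crude-to-adjusted gap was 0.024 points (0.024/0.41 = 0.06 SD), and the SE ratio was 0.99 to 1.00. Under multiple imputation, the identity holds within each completed data set.

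**5. Where it does not cancel.**
- Literal list, no arm-by-time: b moved from 0.248 to 0.131 (compound symmetry) and from 0.221 to 0.171 (unstructured). This is not the planned contrast.
- Covariate measured at each visit, as concurrent BMI would be: 0.770 against 0.811, and 0.520 against 0.606.
- Arms constrained to be equal at T0, in the scenario of step 6: 0.24 SD crude and 0.18 SD adjusted.

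**6. What stays in the estimate.** If the arms differ by δ SD on a covariate that adds γ SD per SD to T1 and T2, the uncorrected part is δ × γ. Both inputs are assumptions.
- δ = 0.5, γ = 0.15/0.41 = 0.37: 0.18 SD.
- δ = 0.6, γ = 0.4: 0.24 SD, or 0.24/0.90 = 27% of the planned effect. With γ = 0.2 it is 0.12 SD; with γ = 0 it is nil.
- Simulating δ = 0.6, γ = 0.4 with no true effect, the mean T1 contrast on complete data was 0.25 SD crude, 0.25 SD with a main effect and 0.01 SD with covariate-by-time terms. With 30% dropout the means were 0.23, 0.23 and −0.02 SD. Gaps in single data sets reached 0.08 SD in a repeat of this scenario.

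If the T0 score itself were flagged and added, the smallest gap with P<.05 is 2.005 × √(2/28) = 0.54 SD. The regression to the mean left in is (1 − r) × 0.54: 0.21 SD at r = 0.6, 0.32 SD at r = 0.4 and 0.11 SD at r = 0.8.

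**The case against.** **The text is condensed.** The article lists variables, omits even the interaction its own contrast needs, and refers to a separate analysis protocol and scripts that are not shown. A reader might infer that the authors decided to enter covariates as main effects only. The documents do not show that. What stands is that the list as printed cannot produce the stated contrast, and that the obvious repair, adding arm-by-time alone, leaves the adjustment inert.

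**The identity is not universal.** A reader might infer that adjusted and crude results must agree in any fit that yields this contrast. They need not: a constrained-baseline model and visit-level BMI both break the identity, and missing outcomes make it approximate. This limits the claim to time-fixed covariates with the arms free at T0.

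**The trial is not biased.** A reader might infer a biased treatment effect. Allocation is randomized (Randomization and Blinding), so the crude contrast is valid over randomizations, and taking change already removes any covariate effect that is constant over time. Only covariates that predict change are left uncorrected. This objection stands in full.

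**The size is assumed.** The imbalance, the covariate effect and the correlation are not in the documents. It is also unclear whether T0 outcome scores are among the variables screened for baseline differences, since the section speaks of baseline values of independent variables and calls the scores dependent. Both points stand. The cancellation does not depend on these inputs, but the 0.2 SD does.

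**Conclusion.** The concern holds in a limited form. Read literally, the listed fixed effects do not estimate the between-arm difference in change. With arm-by-time supplied and the arms free at T0, sex, age, education, baseline BMI and any baseline-difference variable entered as main effects cancel from that difference. They cancel exactly with complete or imputed data and nearly so with the planned 30% dropout. The adjusted models would then add little to the crude one, and their agreement must not be presented as robustness to confounders.

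The loss is correction for a realised chance imbalance in a predictor of change: about 0.2 SD under the assumptions shown, nil if the covariate does not predict change. The primary crude comparison and the sample size are unaffected. The change should be made, but the trial's validity does not turn on it.

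**What to change.** **Preferred.** For the adjusted models, take T1 and T2 as the outcomes. Enter arm, time, arm-by-time, the baseline value of that outcome, and prespecified baseline covariates as fixed effects. State that BMI is the baseline value, not the concurrent one. The baseline outcome must be in the model; without it, the model tests raw T1 and T2 differences. At an assumed correlation of 0.6, the per-person variance is 1.0 for the raw score, 2 × (1 − 0.6) = 0.8 for the change and 1 − 0.6² = 0.64 with the baseline outcome as covariate.

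**Alternative.** Keep T0 as an outcome and add arm-by-time and covariate-by-time terms. This costs about two extra parameters per continuous or binary covariate and more for multi-level education, with about 38 completers planned.

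In either case, do not enter the T0 value of an outcome as a main-effect covariate in a model that also has T0 as an outcome. The cost is about one line in the analysis scripts and a sentence in the plan; no new data are needed.

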### Objectives

Hence, there seems to be a need for a strategy with an eye for everyday life of people with T2DM to promote long-term healthy eating. A health theory centered around the everyday life context is salutogenesis. Applying salutogenesis to nutritional research leads to the assumption that healthy eating is not regarded as a central goal in life but as a resource for greater enjoyment of life [32]. It requires to accept a holistic viewpoint on health and real-life complexity as starting points for conducting and evaluating nutritional interventions. In salutogenesis, health results from the continuous everyday life interactions between the individual and the social, economic, cultural, physical, mental, and biochemical stressors [33]. The central concept in salutogenesis is the sense of coherence (SoC), which is the individual capability to mobilize and use health-promoting resources [33]. Understanding the *resources* that facilitate coping with these stressors in a health-promoting manner can help to unravel underlying principles of creating health [34]. Salutogenesis guided the development of the Salutogenic Intervention for Type 2 Diabetes (SALUD) program [35].

The aim of this study protocol is to outline the randomized controlled trial (RCT) in which the SALUD program is compared with the Dutch usual care for T2DM. The theoretical principle behind the program is mobilizing 2 important psychosocial resources required for organizing healthy eating and improved well-being in everyday life: self-identity and social support [35]. The present hypothesis is that mobilizing these resources will initiate a process of empowerment, leading to improved food literacy (direct effect) and improved health (indirect effects). Food literacy is the capability to navigate different food situations to make healthy eating choices [36], which is important for healthy eating and well-being in the long term. It is a measure that combines all relevant aspects for healthy eating in everyday life, that is, knowledge, skills, and behaviors. Hence, the primary objective is to determine the effect of the SALUD intervention on food literacy. Diet quality as well as several physical and psychosocial outcomes will be evaluated as secondary outcomes.

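### Food literacy is sized for one 5% test at T1 but tested at two visits in several models, with no test named in the article as the one that decides

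*Protocol article*

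**What the plan says.** - **Objective** (Protocol article, Objectives): "the primary objective is to determine the effect of the SALUD intervention on food literacy". No visit is attached. The Abstract and the Quantitative Evaluation section also name food literacy as primary without a time point.
- **Sample size** (Sample Size Calculation): the control assumption is "an anticipated mean of 3.83 (SD 0.41) in the control group is expected at T1", against 4.20 in the intervention group. The result is "With a standard power of 80% and a significance level of 5%, a total of 19 participants per group (38 participants in total) are needed". This is one comparison at one visit.
- **Threshold** (Statistical Analyses): "Two-sided *P* values <.05 are regarded as statistically significant". The sentence covers every test.
- **Visits and models** (Statistical Analyses): the mixed models compare the arms on change from baseline at both T1 and T2. "Multiple models are tested; a crude model, and additional models that are adjusted for confounders commonly adjusted for in literature", and the covariates are introduced by an open list of examples (sex, age, education, BMI). Variables that differ significantly between the arms at baseline also enter a model. The results table is to show P values for the treatment effect for all outcomes.
- **Safeguards** (Randomization and Blinding; Statistical Analyses): an independent, blinded researcher runs the primary analysis, and treatment codes are broken only after the analyses are final. The tests are said to follow a separate analysis protocol, which is not shown.

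**The concern.** The design and the analysis do not describe the same test. The design has one comparison at T1 with all of the 5%. The analysis section has at least six P values for the same outcome: two visits, each in a crude model and at least two adjusted ones. The plural in the text gives three models even if the baseline-difference model counts as one of the additional models. Its covariates depend on the observed data, so that model cannot be fixed in advance.

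Two things are at stake. First, if a favourable result at either visit or in any model could be read as showing an effect, the chance of a false claim is higher than the 5% used to size the trial. Second, the results may conflict, for example significant at T1 in the crude model but not at T2 after adjustment, and the article gives no rule for which one is the trial's answer.

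**Working it through.** **Step 1. The plan's own figure.** Inputs from the Sample Size Calculation: difference 4.20 - 3.83 = 0.37, SD 0.41, two-sided alpha 0.05, power 0.80.

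- Effect size: 0.37/0.41 = 0.902, in line with the stated 0.9.
- n per group = 2 x [(1.960 + 0.842) x 0.41/0.37]^2 = 19.28. Rounded up this is 20 (21 with the t distribution). The stated 19 is the same figure rounded down.
- Dropout: 19/(1 - 0.30) = 27.1, so 28 per group and 56 in total, as stated.

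The size is reproduced within rounding, and it assumes one test at 5%.

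**Step 2. Two visits, one model.** The chance of at least one |z| > 1.96 under no effect is 1 - P(|z1| < 1.96 and |z2| < 1.96), with (z1, z2) bivariate normal. The article gives no correlation, so it is varied:

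| Assumed correlation of the two tests | Chance of at least one P<.05 |
|---|---|
| 0 | 9.75% |
| 0.3 | 9.5% |
| 0.5 | 9.1% |
| 0.7 | 8.3% |
| 0.8 | 7.8% |

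The tests concern change from baseline, so T1 and T2 share the baseline value. With equal correlation r between all visits, the correlation of the two change scores is (1 - r)/[2(1 - r)] = 0.5 whatever r is, which gives 9.1%. If T1 and T2 are closer to each other than to baseline, the correlation is higher and the rate is lower.

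**Step 3. Several models.** This was simulated under no effect, 5,000 trials per setting. The three models were crude; four fixed covariates; and covariates differing at baseline at P<.05, out of ten plus the baseline score. Each visit was fitted by ordinary regression of change from baseline, in place of the mixed model. Assumptions: visit correlation 0.5 or 0.7; covariates explain 0 or 30% of the variance of change; 19 or 28 per group.

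| What may count | Chance of at least one P<.05 |
|---|---|
| Crude model, T1 only | 4.6-5.2% |
| Crude model, T1 or T2 | 8.6-9.4% |
| Three models, T1 only | 6.8-7.6% |
| Three models, T1 or T2 | 12.4-13.3% |

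The simulation error at 13% is about sqrt(0.13 x 0.87/5000) = 0.5 percentage points. With other numbers of screened variables and other model choices, the last row moves over roughly 11-15%, and the three-model rate at T1 stays near 7-8%. Six independent tests would give 1 - 0.95^6 = 26.5%, but these P values are strongly correlated. With 11 independent screened variables, none differs at P<.05 in 0.95^11 = 57% of trials, and the screened model then repeats the crude one.

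**Step 4. If both visits were meant to decide.** With a Bonferroni split (0.025 each), n = 2 x [(2.241 + 0.842) x 0.41/0.37]^2 = 23.3, so 24 per group (25 with the t distribution). After 30% dropout this is 35-36 per group, or 70-72 in total. At 0.025, the stated 19 per group has about 71% power (67% with the t distribution).

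**The case against.** The strongest reply is that the point may already be settled elsewhere. The article cites a separate analysis protocol, and a journal article normally leaves the primary model and the exact covariate list to such a document. This stands as a limit on the finding. It does not remove it, because the article itself commits to several models at two visits under one threshold, and to one covariate set chosen from the data.

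Second, T1 is less open than T2: the trial is sized at T1, and T2 is labelled follow-up. This also stands in part. A planning assumption is not a decision rule, and the analysis section tests both visits alike. Even with T1 taken as fixed, the choice among models remains, at about 7-8%.

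Third, crude and adjusted models side by side are ordinary reporting. That is true, but the article does not call any of them the main model or a sensitivity analysis.

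Two stronger readings are tempting. A reader might infer that the 5% level is in fact broken. The article sets a threshold for calling a P value significant; it nowhere says that one significant visit or model makes the trial positive, so the inflation is conditional. A reader might also infer that unblinded researchers, who write the scripts, are free to pick among the results. The documents do not support that: the primary analysis is run blinded by an independent researcher, and codes are broken afterwards. This limits the choice during the analysis. It does not say which P value is the trial's answer once the codes are known.

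**Conclusion.** The point holds in conditional form. The article sizes food literacy for one 5% test at T1, describes at least six tests of it at P<.05, and names none as deciding. If any significant result could support the claim of effect, the false-positive rate is about 7-8% (T1 only, three models), 8-10% (two visits, one model) or 11-15% (both). The direction follows from the text. The size rests on correlations, covariate strength and a number of screened variables that the article does not give, and on ordinary regression standing in for the mixed model. The documents do not show that the level is actually exceeded, and the unseen analysis protocol may already name the test.

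**What to change.** Before the treatment codes are broken:

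1. Name one primary test: the between-arm contrast in SPFLS total score at T1, the visit used for the sample size, from one prespecified mixed model. State which model term carries it. The fixed effects listed are treatment, time and covariates, while separate contrasts at T1 and T2 need a treatment-by-time term.
2. Close the covariate list of that model, and do not choose its covariates by baseline significance tests.
3. Label T2 as follow-up, and the crude and other adjusted models as sensitivity analyses that cannot change the conclusion.
4. If the cited analysis protocol already fixes these points, quote it in the report.

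The cost is wording only. Every planned analysis can still be reported, and 19 per group (28 with dropout) stands within rounding. Keeping both visits as deciding tests would instead need the split alpha and the 70-72 participants shown above.

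### Choosing covariates by significance tests of baseline differences selects on chance and adds a data-dependent model to a set in which none is named primary

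*Protocol article*

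**What the plan says.** All of this is in the Statistical Analyses section of the protocol article.

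- **Baseline tests.** Chi-square and t tests "are used to compare the descriptive statistics between study groups and to identify potential covariates". The general threshold is: "Two-sided *P* values <.05 are regarded as statistically significant".
- **Use of the tests.** "Variables that statistically significantly differed at baseline are also included in a model as covariates".
- **Other models.** "Multiple models are tested; a crude model, and additional models"; the latter are described as "additional models that are adjusted for confounders commonly adjusted for in literature (eg, sex, age, education, and BMI"). The list opens with an eg, so it is not closed. No model is named as the primary one.
- **Baseline value of the outcome.** The contrast of interest is change from baseline at T1 and T2, and "random effects are the repeated measures per participant at T0, T1, and T2". T0 is therefore part of the response in every model, including the crude one.

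**The concern.** In a randomised trial, a significant baseline difference is a chance event (unless the allocation was faulty). The test carries no information on whether the variable predicts the outcome, and that is what decides whether adjusting for it helps. Two errors follow. A variable unrelated to food literacy can be added, and a moderate imbalance in a strong predictor can fall short of significance and stay out of that model.

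The content of this model is also unknown until the data have been seen. It then stands beside a crude model and several others with nothing to say which one answers the primary question. At stake are the interpretability of the primary result and the type I error of the set of models taken together.

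**Working it through.** **Inputs from the document.** Means 4.20 and 3.83, SD 0.41, 80% power, two-sided 5%, 19 per group before and 28 after 30% dropout (Sample Size Calculation). Baseline variables: the Participant Characteristics section lists age, living situation, ethnicity, education, disease duration, medication use and smoking; sex and the baseline outcomes could be added. The number to be tested is not stated, so 8 to 15 is an assumption.

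**1. The plan's own figure.** d = (4.20 − 3.83)/0.41 = 0.902. The normal formula 2(1.960 + 0.842)²/d² gives 19.3 per arm, against the stated 19. Then 19/(1 − 0.30) = 27.1, so 28 per arm and 56 in total. The stated figures are reproduced to within rounding, and nothing below changes them.

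**2. Chance of at least one flag.** For k independent variables it is 1 − 0.95^k:

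| k | at least one flagged |
|---|---|
| 8 | 34% |
| 10 | 40% |
| 15 | 54% |

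Correlated variables (weight, BMI and waist-hip ratio; self-efficacy, sense of coherence and quality of life) would lower these figures.

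**3. What the rule can miss.** With 28 per arm, a continuous variable is flagged only if the arms differ by more than 2.005 × √(2/28) = 0.54 SD. Take an imbalance of 0.5 SD in a predictor with an assumed correlation of 0.5 with the outcome. It is not flagged, yet it shifts an unadjusted comparison of follow-up scores by 0.5 × 0.5 = 0.25 SD, which is 0.25/0.90 = 28% of the planned effect.

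**4. Simulation.** 10,000 trials per setting, 10 independent normal baseline covariates of which one is prognostic (correlation r with the outcome), one follow-up time, complete data, 19 per arm. The rule flagged at least one covariate in about 40% of trials and the prognostic one in about 5%.

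| | crude | significance-selected | fixed in advance | any of the three |
|---|---|---|---|---|
| Type I error, r = 0.5 | 5.5% | 4.6% | 5.1% | 8.2% |
| Type I error, r = 0.7 | 5.0% | 3.7% | 4.8% | 8.6% |
| Power at d = 0.9, r = 0.5 | 76% | 74% | 87% | – |
| Power at d = 0.9, r = 0.7 | 78% | 76% | 96% | – |
| SD of estimate (no effect), r = 0.5 | 0.33 | 0.33 | 0.29 | – |

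With 28 per arm and r = 0.5, the type I error was 4.2% for the selected model and 7.5% for any of the three.

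**5. What handling of the baseline outcome is worth.** This is separate from the selection rule, but it bears on the fix. With complete data, equal variances and baseline means left free by arm, a change-from-baseline contrast has variance proportional to 2(1 − r), where r is now the correlation between baseline and follow-up. Baseline adjustment gives 1 − r². Two-sided t-test power at 19 per arm, d = 0.902:

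| assumed r | change from baseline | baseline-adjusted |
|---|---|---|
| 0.3 | 63% | 81% |
| 0.5 | 77% | 88% |
| 0.7 | 94% | 97% |

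The document gives no correlation, so only the range is informative.

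**The case against.** The strongest reply is that the significance rule is one layer of a wider plan. The crude model stands whatever the baseline tests show. Sex, age, education and BMI enter other models on literature grounds, and T0 is a repeated measure throughout. Much of this is right, and it rules out three stronger readings that a reader might infer.

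- *The plan neglects prognostic covariates or leaves the baseline outcome to chance.* It does not. Three useful covariates are named and baseline food literacy is in every model. What remains is that the list is open and no model has priority.
- *The rule by itself inflates the type I error.* In simulation the selected model, taken alone, is slightly conservative. The excess arises only if the result may be taken from any of several models.
- *The power gain from baseline adjustment measures the harm of the rule.* It does not. The gap in step 5 is between a change score and baseline adjustment. It depends on an unstated correlation, and a mixed model with equal baseline means across arms would recover essentially all of it.

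The reply does not rescue the rule. It still selects on chance, and it still adds a model whose content the data decide. Nor is this a detail left to an unseen analysis plan: the article states the rule outright.

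**Conclusion.** The point holds in this limited form. Selection by baseline significance tests gives no useful precision, can pass over a prognostic imbalance, and makes one of several candidate models data-dependent. The chance of at least one spurious flag is 34% to 54% for an assumed 8 to 15 independent variables, and less with correlation. The type I error is about 8% to 9% at 19 per arm only if the crude, selected or fixed-covariate model may each be reported as the result. That figure rests on the simulation's assumptions: independent normal covariates, one prognostic, a single time point and no missing data. The change should be made, but the defect does not invalidate the trial's design or its sample size.

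**What to change.** 1. Delete the sentence that enters significantly different baseline variables into a model, and the use of baseline tests to find covariates. Describe baseline by arm.
2. Before the treatment codes are broken, name one primary mixed model with a closed covariate list: age, sex and education.
3. Use baseline food literacy once. Either keep T0 in the response with baseline means set equal across arms, or take T1 and T2 as responses with the baseline score as a covariate. Adding the baseline score as a covariate while T0 stays in the response would use it twice.
4. Label the crude model and all other adjusted models as sensitivity analyses.

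Cost: a few sentences and a small change to the model script. No new data are needed, since age and education are on the screening questionnaire, sex is already a planned covariate and the outcome is measured at T0. The total stays at 56. The article's Results section places the data analysis still ahead.
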